**Methods/design:**

A two-arm, parallel design randomized controlled trial in 300 2-to 6-year-old children with overweight and obesity from Romania, Spain and Sweden (*n* = 100 from each). Following baseline assessments children are randomized into the intervention or control group in a 1:1 ratio. The intervention, the ML program, consists of 10-weekly group sessions which focus on evidence-based parenting practices, followed by the previously validated MINISTOP application for 6-months to support healthy eating and physical activity behaviors. The primary outcome is change in body mass index (BMI) z-score after 9-months and secondary outcomes include: waist circumference, eating behavior (Child Eating Behavior Questionnaire), parenting behavior (Comprehensive Feeding Practices Questionnaire), physical activity (ActiGraph wGT3x-BT), dietary patterns (based on metabolic markers from urine and 24 h dietary recalls), epigenetic and gut hormones (fasting blood samples), and the overall acceptance of the overweight and obesity management in young children (semi-structured interviews). Outcomes are measured at baseline and after: 10-weeks (only BMI z-score, waist circumference), 9-months (all outcomes), 15- and 21-months (all outcomes except physical activity, dietary patterns, epigenetics and gut hormones) post-baseline.

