### Aim

The overall aim of this study is to assess the feasibility, acceptance and effectiveness of an overweight and obesity intervention in a socially diverse population of families. The specific aims are:To determine the effectiveness on child weight status (BMI z-score) of a 10-week parent support program delivered in groups focusing on evidence-based parenting practices (the ML program) followed by a mHealth component for 6-months (the MINISTOP application, app) for overweight and obesity in preschool-aged children.To assess change in secondary outcomes, which are: waist circumference, child eating behavior, parental feeding practices, and physical activity.To assess epigenetic mechanisms and physio pathological processes underlying childhood obesity including the role of gut hormones.To assess and validate child food intake with metabolic markers in urine metabolomics.To evaluate the feasibility of recruitment (facilitators and barriers), attrition and acceptability of the ML program, the standard treatment and the overall acceptance of overweight and obesity management according to patients and care providers.

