### Randomization and blinding

After the consent form has been signed, the participants are randomly allocated to either the intervention group (parent support program and mHealth booster) or the control group (standard care as per country) at a 1:1 ratio via a random allocation sequence list (in blocks of three). The sequence list was generated using free software environment for statistical computing and graphics R (version 3.5.1) [35]. The random allocation sequence is managed by a person who has no relationship with recruitment or treatment and opaque envelopes are used to ensure concealment. Those assessing the outcomes are blinded to the treatment allocation; however, owing to the nature of the intervention participants are not blind to their allocation.

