### Intervention

#### The More and Less program

The ML program is based on the Keeping Foster and Kin Parents Supported and Trained (KEEP) parenting program, which has been tested in multiple settings [36–39]. KEEP is based on Bandura’s Social Learning Theory [40] and Patterson’s Social Interaction Learning Theory [41, 42]. The key concept of the programs is to support parents in evidence-based parenting practices, especially regarding positive reinforcement and limit setting, in order to improve parent and child communication. In ML, the improved communication lays the foundation for parents to support a healthy lifestyle for the child.

The ML program is comprised of 10 weekly sessions (1.5 h/week) and is culturally adapted for Romanian, Spanish, and Swedish families with preschool aged children with overweight or obesity. Table 1 displays the content of the ML program [7, 30]. Beyond the evidence-based parenting practices, the program includes content regarding healthy food habits, physical activity habits, as well as techniques to help parents regulate emotional control. Each session begins with a theoretical introduction to a parenting skill, the focus of the session is then discussed and practice is done through role play and homework assignments. To facilitate the implementation of the ML program it follows a manual where the sessions are described with precise instructions to the group leaders (2 per group). The parents receive a manual which summarizes what has been discussed during each session. For parents who are unable to attend sessions, the parental manual is sent home to the family and the family is contacted by phone for a brief review of the session. To facilitate session attendance the time and location for the groups are planned to suit the parents. Child care is also provided during the sessions.

**Table 1 Tab1:** Session content of the More and Less program and themes included in the MINISTOP app

*More and Less Parenting Program*	
Session	Content
1	Welcome and overview
2	Food and play: When more? When less?
3	Parents as teachers: cooperation and energy balance
4	Parents as teachers: to teach children new behaviors
5	Rewards and incentives
6	Pre-teaching
7	Parents as teachers: limit setting strategies
8	Power struggles: to avoid and to handle them
9	More support – Less stress
10	Summary: parenting, food and play – to prepare for the future
*MINISTOP app*	
Theme	Content
1	Healthy foods in general
2	Breakfast
3	Healthy small meals

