### Control

The weight management offered to the control group follows the standard care procedure for each country of participation. In Romania and Spain, the control group receives an evaluation of a one-day food frequency questionnaire as well as a 30-min consultation with a doctor that is a specialist in childhood nutrition, where healthy lifestyle recommendations are made. The parents also receive a hand-out which provides general recommendations for healthy food and physical activity in 2 to 6 year olds. Furthermore, in Romania the children are re-evaluated after 3 months during a 15-min consultation. In Sweden, the control group receives standard care according to the Action plan for overweight and obesity for Stockholm County [44]. Children with overweight and children with obesity younger than 4 years receive support from their child health care nurse. Children older than for 4 years with obesity are followed in an outpatient pediatric clinic with yearly visits to a pediatrician and follow-up visits to a pediatric nurse, approximately 5 visits (30 min in duration) per year [7]. The treatment centers around supporting the family in creating healthy diet and physical activity habits for the child. Children may also be referred to dieticians, psychologists or physiotherapists.

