### Statistical analysis

Intention-to-treat analysis using generalized linear mixed models with repeated measures will be used to examine the effects of the intervention on primary (aim 1) and secondary outcomes (aim 2) for the total study population (i.e., all three sites). The link function for the primary outcome (BMI z-score) will be the identity and the Gaussian family (equivalent to a linear regression). In secondary outcomes we will use a Gaussian identity and family link function for waist circumference, physical activity and sedentary behavior, and a logarithmic link and Poisson family function (equivalent to a Poisson regression) for child eating behavior and parental feeding practices. A random effect for country will be used to account for the clustered study design. In the models, we will control for relevant covariates such as sex, age, parental weight status, education level, income and foreign background. Random intercept and a random slope for time will be included in the model to control those non-observed confounders specific to each child that could be constant or vary in time, respectively. Furthermore, interactions between variables will be estimated. If missing values in the outcomes (primary and secondary) are more than 10%, these will be imputed through a two-part model (also known as a model for semi continuous data). In this model, we would simultaneously estimate the probability of not being missing (first part) and the outcome (second part), using a mixed generalized linear model, in which we would include, as explanatory variables: age, sex, parental weight status, foreign background, educational level, and the random effects which are aforementioned.

Statistical tests and analyses of the interaction of phenotypical outcomes with epigenetics will include Manhattan plots, volcano plots, principal component analysis (PCA)/cluster, heatmaps, partial least square-discriminant analysis (PLS-DA), correlations and association studies, linear regression models, receiver operating characteristic (ROC) curves and these will be implemented as appropriate.

The means and medians for the gut hormone values before and after the intervention will be compared, using Student’s t test and Mann-Whitney U test, respectively. The differences will be adjusted in a generalized linear mixed model, with an identity link and Gaussian family, including the confounders, both observed and unobserved, indicated above.

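### The model puts clustering at country level, but the clustering that can bias the standard error sits in the intervention arm's parent groups, which have no term

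*Protocol article*

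**What the plan says.** Allocation is described at the level of the participant: "the participants are randomly allocated to either the intervention group (parent support program and mHealth booster) or the control group" (Randomization and blinding).

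The intervention is a "10-week parent support program delivered in groups focusing on evidence-based parenting practices" (Aim). The section on the More and Less program gives ten weekly sessions of 1.5 hours, with discussion and role play, run by two leaders per group. Six months of app use by each family follow.

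For controls, "The weight management offered to the control group follows the standard care procedure for each country of participation" (Control). That section describes consultations and nurse or clinic visits, and no group format.

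On the model, Statistical analysis says "A random effect for country will be used to account for the clustered study design". It adds: "Random intercept and a random slope for time will be included in the model to control those non-observed confounders specific to each child". No term for parent group or leader is named. The sample size section gives 75 children per group, after adjustment for drop-out, for 85% power to detect 0.3 BMI z-score at 9 months. It mentions no design effect.

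**The concern.** This is a partially nested design: individuals are randomised, but one arm is then treated in clusters. Children whose parents share a group and its leaders may have more similar outcomes than children from different groups. Each intervention child then carries less independent information than the model assumes.

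The terms in the model do not deal with this. Country is crossed with treatment, so its effect removes differences in level between countries but not correlation among families in the same ML group. The child-level intercept and slope are independent between children, so they cannot carry it either.

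The protocol does more than leave the matter open. It recognises clustering and names the level meant to handle it, so an analysis plan that followed this sentence would carry the problem forward. At stake is the primary comparison of BMI z-score at 9 months: confidence intervals that are too narrow and a false-positive rate above nominal, in a trial whose positive result is meant to support routine use.

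**Working it through.** **Inputs from the protocol article.** Difference 0.3, power 85%, 75 per group after drop-out adjustment (Sample size and power calculation); 300 children at 1:1, so about 150 per arm (Participants; Randomization and blinding).

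**Inputs not stated, so assumed.** Two-sided alpha 5%; group size m from 5 to 10; ICC from 0.02 to 0.10, with 0.01 shown for comparison.

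**Step 1: the plan's own figure.** The 75 cannot be strictly reproduced, because SD, alpha and drop-out rate are not given. Solving backwards, SD = 0.3 / ((1.960 + 1.036) × √(2/n)). With n = 75 (no drop-out) this gives 0.613; with n = 60 (20% drop-out), 0.548. Forwards, SD 0.55 needs 61 per group, or 77 with 20% drop-out. So 75 is plausible as a calculation for independent observations, with no allowance for clustering.

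**Step 2: variance.** Design effect in the intervention arm: DE = 1 + (m − 1) × ICC. The control arm keeps 1. The ratio of true to assumed variance of the difference is r = (1 + DE)/2. For m = 8 and ICC 0.05: DE = 1 + 7 × 0.05 = 1.35; r = 2.35/2 = 1.175.

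**Step 3: type I error of the planned test.** 2 × (1 − Φ(1.960/√r)). For r = 1.175: √r = 1.084, 1.960/1.084 = 1.808, giving 7.1%.

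**Step 4: power once groups are modelled.** At 75 per group: Φ(2.996/√r − 1.960). At 150 per arm, with the same proportional drop-out: Φ(2.996 × √2/√r − 1.960).

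| m | ICC | DE | r | Type I error, groups ignored | Power at 75, groups modelled | Power at 150, groups modelled |
|---|---|---|---|---|---|---|
| 5 | 0.01 | 1.04 | 1.020 | 5.2% | 84.3% | 98.7% |
| 10 | 0.01 | 1.09 | 1.045 | 5.5% | 83.4% | 98.6% |
| 5 | 0.02 | 1.08 | 1.040 | 5.5% | 83.6% | 98.6% |
| 8 | 0.05 | 1.35 | 1.175 | 7.1% | 78.9% | 97.4% |
| 10 | 0.10 | 1.90 | 1.450 | 10.4% | 70.1% | 94.1% |

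The number per arm that restores 85% power is 75 × r: 78 at r = 1.04 and 109 at r = 1.45, both below 150.

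**Step 5: does the country term help?** A simulation used three countries, 50 children per arm in each, one outcome per child, a country-adjusted comparison that ignores parent group, and 20,000 replicates per setting. At ICC 0 it returned 4.9% to 5.0%. At ICC 0.05 it returned 6.1% for groups of up to 6 and 7.7% for groups of 10; at ICC 0.10, 7.8% and 10.0%. Adjusting for country does not remove the excess.

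The power figures use normal quantiles. With about 15 to 30 groups in the intervention arm (150/10 to 150/5), small-sample degrees of freedom would lower them a little.

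**The case against.** The strongest reply is that the harm is conditional. The documents give neither group size nor ICC, and some features may keep the ICC low. Groups last ten weeks, each family then uses the app on its own for six months before the 9-month endpoint, and missed sessions are covered by a manual and a phone call. This stands: a reader might infer that the error rate is certainly inflated, and the documents do not show that. What they show is a model that gives no protection if the ICC is positive.

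A reader might also infer that the planned test loses power to 79%. It does not. That figure belongs to the analysis that models groups, at 75 per group. The planned test, with its understated standard error, would reject with probability Φ(1.036/√1.175), about 83%, and about 80% at r = 1.45. Nor is the trial underpowered: the plan recruits twice the 75 per group and analyses all sites together.

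Two further readings lack support. The protocol does not say that randomisation is stratified by country, so the point cannot rest on that. Treating country as random with three levels is a modelling preference: treatment is crossed with country, so the choice has little effect on the contrast, and interactions are planned.

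Finally, a condensed article may leave details to a fuller plan. That is fair for the degrees-of-freedom method or an ICC value, but not for the clustering level, which the article chooses itself. Controls may also share doctors, nurses or clinics, so treating them as unclustered is an assumption of the remedy.

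**Conclusion.** The point holds in conditional form. The plan names country as the level that accounts for clustering, while the clustering relevant to the treatment comparison arises in the intervention arm's parent groups and has no term. For any positive group ICC, the standard error of the primary comparison is understated.

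Under the assumed ranges the type I error is about 5.5% to 10.4%, against a nominal 5%; at ICC 0.01 it is only 5.2% to 5.5%. The type I error here refers to an average effect of zero with outcomes still varying between groups. The direction is firm; the size rests on two quantities the documents do not give. With groups modelled, power at 75 per group would be about 84% down to 70%, but at 150 per arm about 94% or more. The matter is therefore the validity of the test and intervals, not the number of children. It should be corrected before analysis.

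**What to change.** Record the ML group to which each intervention family is assigned. Add to the primary model a random effect for parent group in the intervention arm only, with controls as singletons, so that correlation between children in the same group is carried at the follow-up visits. Keep children in their assigned group whatever their attendance, to respect intention to treat. Use Kenward-Roger or Satterthwaite degrees of freedom. Restate the power with an assumed group size and ICC. The country term can stay as it is.

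The cost is one recorded variable and one variance component, with somewhat wider intervals and fewer degrees of freedom. No extra children, visits or procedures are needed. Group membership is easiest to capture while groups are still being formed. If the ICC proves close to zero, the result will hardly change.

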##### Physical activity and sedentary behavior

The ActiGraph wGT3x-BT accelerometer (ActiGraph Corp, Pensacola, USA, www.actiGraphcorp.com) is used to assess physical activity and sedentary behavior over seven consecutive 24 h periods. The ActiGraph will be attached the child’s non-dominant wrist and be worn at all times, except for water-based activities (e.g., showering/bathing or swimming). The recorded movements will be used to estimate time in various activity levels based on appropriate cut-points.

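### The random intercept plus random slope is over-parameterised for outcomes measured only at baseline and 9 months (gut hormones, and physical activity if there is one value per visit)

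*Protocol article*

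**What the plan says.** The Statistical analysis section plans generalized linear mixed models with repeated measures for the primary and secondary outcomes, and adds: "Random intercept and a random slope for time will be included in the model to control those non-observed confounders specific to each child". It does not say whether the intercept and slope may be correlated.

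For the secondary outcomes, "we will use a Gaussian identity and family link function for waist circumference, physical activity and sedentary behavior", so a residual variance is estimated as well. The adjusted gut-hormone comparison is also a Gaussian identity-link mixed model, "including the confounders, both observed and unobserved, indicated above". The only unobserved confounders mentioned before that sentence are those assigned to the random intercept and slope, so the gut-hormone model takes over both.

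The Abstract limits the 10-week visit to BMI z-score and waist circumference, and gives the later visits as "15- and 21-months (all outcomes except physical activity, dietary patterns, epigenetics and gut hormones) post-baseline". Table 2 agrees: accelerometry and fasting blood have marks at baseline and 9 months only. The accelerometer "is used to assess physical activity and sedentary behavior over seven consecutive 24 h periods" at each of those visits; whether the model uses daily values or one summary per visit is not stated.

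**The concern.** A random slope describes how children differ in their change over time, beyond measurement noise. With one value at each of two visits, a child's change is a single difference, and nothing in the data separates a true difference in slope from residual error. The plan nevertheless asks for both.

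At stake is the prespecification of the physical-activity and gut-hormone analyses. If the stated model stops with an error, or returns variance components that depend on the optimiser, the analysts must choose a replacement once the data are in hand. Blood sampling is optional (Adverse events section), so children with only one sample are likely. They contribute two random effects and a single observation.

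The stated reason for the random effects is also wrong. Random effects are assumed independent of the covariates. They model correlation within a child and do not remove unobserved confounding.

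**Working it through.** The article gives no variances for these outcomes, so there is no figure of its own to reproduce. The visit times (0 and 9 months), the random-effects rule and the Gaussian family come from the article. All variances and correlations below are assumptions for illustration.

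**Counting parameters.** Let a be the intercept variance, b the slope variance, c their covariance, e the residual variance, and T = 9 months:

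- Var(baseline) = a + e
- Cov(baseline, 9 months) = a + cT
- Var(9 months) = a + 2cT + bT² + e

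That is three equations in four unknowns. Lowering e by d, raising a by d, lowering c by d/9 and raising b by 2d/81 leaves all three unchanged.

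**Example, with d = 0.03.**

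| | a | b | c | e |
|---|---|---|---|---|
| Set 1 | 0.20 | 0.0010 | 0 | 0.05 |
| Set 2 | 0.23 | 0.00174 | −0.00333 | 0.02 |

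- Set 1: Var(baseline) = 0.20 + 0.05 = 0.25; Cov = 0.20; Var(9 months) = 0.20 + 0.0010 × 81 + 0.05 = 0.331.
- Set 2: Var(baseline) = 0.23 + 0.02 = 0.25; Cov = 0.23 − 0.03 = 0.20; Var(9 months) = 0.23 − 0.06 + 0.141 + 0.02 = 0.331.

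The likelihood cannot tell the two sets apart, although the residual variance differs by a factor of 2.5.

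**Independent random effects (c = 0).** Three parameters meet three moments, so the model is just identified. Then 81b = Var(9 months) − Var(baseline), which requires the 9-month variance to be at least the baseline variance. Placing time zero at 9 months reverses that requirement.

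**What software does.** Data were simulated for 300 children with two visits and assumed variances.

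- R lme4 stopped on the correlated model: 600 observations against 600 random effects.
- R nlme returned a fit with a 95% interval for the residual SD from 0.0016 to 94.
- On a second simulated set, five optimisers in Python statsmodels reached the same log-likelihood (−803.4254) with residual variances from 0.301 to 0.334.
- With c = 0, both R packages fitted normally.

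**Effect on the arm comparison.** With two visits, the four-parameter model is a redundant way of writing an unstructured 2×2 covariance matrix. The arm-by-time estimate and its standard error depend only on that matrix, which is identified. In the second simulated set (balanced and complete), the estimate was −0.5286 (SE 0.1115) under the correlated, independent and intercept-only models and under a plain change-score comparison.

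**Other outcomes.** The same rank check finds all four parameters identified with four visits (CEBQ, CFPQ), with five visits (BMI z-score, waist circumference), and with seven daily activity values at each of two visits.

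**Precision of a baseline-adjusted comparison.** With equal variances σ² and correlation ρ, the ANCOVA variance σ²(1 − ρ²) divided by the change-score variance 2σ²(1 − ρ) is (1 + ρ)/2. This is 0.85 at ρ = 0.7 and 0.75 at ρ = 0.5, so 15–25% lower. In the example matrix, ρ = 0.20/√(0.25 × 0.331) ≈ 0.70. The change-score variance is 0.25 + 0.331 − 0.40 = 0.181 and the ANCOVA variance is 0.331 − 0.20²/0.25 = 0.171. The ratio is 0.945, a reduction of about 5.5%.

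**The case against.** A reader might infer that the physical-activity and gut-hormone models cannot be fitted at all. The article does not support that.

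- It never prescribes a free intercept-slope covariance, and a condensed article may leave that detail to the analysis plan. With independent effects the model fits. It does so only just, under the variance constraint shown above, and nothing in the article says that this version is intended.
- Seven days are recorded per visit, so a day-level activity model would be identified. This stands for activity. It does not help gut hormones, for which no replicate sample within a visit is described.
- Actual visit dates, if they vary, identify the four parameters weakly. With an assumed spread of 2 to 4 weeks (SD), the standard error for a residual variance of 0.40 is 0.46 to 0.21.

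A reader might also infer a biased treatment effect. That does not follow: the parameters that cannot be separated are nuisance components, and the arm comparison rests on the identified covariance matrix. Nor does the confounding claim threaten that comparison, because allocation is randomised.

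Finally, the precision gain comes from using the baseline value, not from dropping the slope. It should not be read as the cost of the present wording, particularly as the article does not say how baseline enters the model.

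**Conclusion.** The point holds in limited form. The random-effects rule is unsuitable for outcomes with one value at each of two visits: four variance parameters for three moments if intercept and slope may correlate, and only just identified if they may not. It applies to gut hormones, and to physical activity and sedentary behaviour if each visit is summarised as one value.

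The consequence is a prespecified model that may have to be replaced after the data are seen, not a biased result. The primary outcome, waist circumference, CEBQ and CFPQ are untouched. The conclusion assumes nominal visit times and takes the gut-hormone sentence to carry over both random effects. The sentence on unobserved confounders is a separate error of rationale. Because a stated rule is unsuitable and the correction is specific and cheap, it is worth making.

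**What to change.** Reserve the random slope for outcomes with at least three visits. For outcomes measured only at baseline and 9 months, prespecify one of the following:

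- ANCOVA of the 9-month value on arm, baseline value, country and the planned covariates; or
- a mixed model with an unstructured 2×2 covariance and a common baseline mean in the two arms.

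State whether accelerometry enters as one summary per visit or as daily values. The imputation model reuses the same random effects, so its wording should follow the change.

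Replace the claim that random effects control unobserved confounders, including its repetition in the gut-hormone paragraph. Say instead that they model correlation within a child, and that randomisation protects the arm comparison.

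The cost is analysis wording only; no data collection changes. Plain ANCOVA has one small drawback: it drops children without a 9-month value unless they are imputed. The mixed-model version keeps them.

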For the validation of child food intake with metabolic markers in urine, the urinary dietary model will be derived using previously described methodology [29]. Comparison between the study groups will be carried out using PCA and Monte Carlo cross-validated partial least square-discriminant analysis (MCCV-PLS-DA) methodology. The relationship between dietary biomarkers and the dietary metabolite profile will be carried out using a generalized linear mixed model, with an identity link and Gaussian family, including, again, the confounders.

The semi-structured interviews with parents and health care professional will be fully transcribed verbatim and analyzed using thematic analysis [57].

For our analyses we will use R [35], STATA version 12.1 (StataCorp 2011, College Station, TX, USA) and SPSS Statistics (IBM, Armonk, NY, USA).

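### Random intercepts and slopes do not control unobserved confounders, and the gut-hormone analysis, written as before/after, relies on the claim that they do

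*Protocol article*

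**What the plan says.** All the relevant text is in the Statistical analysis section of the protocol article, with the visit schedule in the abstract and Table 2.

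- **Main models (aims 1 and 2).** The mixed model for the effect of the intervention adjusts for listed covariates (sex, age, parental weight status, education, income, foreign background). It also has a random intercept and a random time slope, whose stated purpose is "to control those non-observed confounders specific to each child that could be constant or vary in time, respectively". The sentence thus assigns the intercept to constant confounders and the slope to time-varying ones.
- **Gut hormones (aim 3).** "The means and medians for the gut hormone values before and after the intervention will be compared". The tests named are Student's t and Mann-Whitney U. A Gaussian mixed model then adjusts the differences, described as "including the confounders, both observed and unobserved, indicated above". No arm contrast is stated.
- **Dietary biomarkers (aim 4).** "The relationship between dietary biomarkers and the dietary metabolite profile will be carried out using a generalized linear mixed model". Adjustment is given only by back-reference: "including, again, the confounders". The word for unobserved is not repeated here.
- **Visits.** Gut hormones are measured at baseline and 9 months only. The abstract excludes them later: "15- and 21-months (all outcomes except physical activity, dietary patterns, epigenetics and gut hormones) post-baseline". The Adverse events section makes blood sampling optional.

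**The concern.** A random effect is assumed to be independent of the covariates in the model. An unobserved confounder is by definition related to the exposure, so it violates that assumption and is not removed. A random slope lets children differ in their trend over time. It does not adjust for an unmeasured factor that changes over time and affects the outcome.

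The sentence therefore claims protection that the model cannot give. Where arms are compared, randomisation supplies that protection and nothing is lost. The gut-hormone analysis is not written as an arm comparison, so randomisation is not used there and the stated adjustment is the only safeguard. At stake is whether a 9-month change in hormone levels in growing 2- to 6-year-olds is read as an intervention effect already cleared of unobserved confounding.

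**Working it through.** The plan states no figure on this point, so there is none to reproduce. The check has three parts.

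**1. What a before/after contrast estimates.** Write child *i*'s hormone value as

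- baseline: Y₀ = aᵢ + e₀
- 9 months: Y₁ = aᵢ + δ + sᵢ + τ·Zᵢ + e₁

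Here aᵢ collects everything constant within the child. δ is the average change without the intervention (growth, secular trend, regression to the mean). sᵢ is the child's own departure from δ, with mean zero. Zᵢ is 1 in the intervention arm and 0 in the control arm, and τ is the effect of the intervention against standard care.

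- Mean change in the intervention arm: δ + τ
- Mean change with both arms pooled 1:1: δ + τ/2
- Mean change in the control arm: δ
- Difference between arms: (δ + τ) − δ = τ

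The term aᵢ cancels in every line. That comes from pairing, not from the random intercept. In one simulated complete data set (300 children, two visits, true change −0.3), the random-intercept time coefficient and the mean paired difference were both −0.292. The random slope absorbs sᵢ, which has mean zero. The common part δ stays in the fixed time effect. Only the arm comparison removes it.

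**2. Size of δ.** The article gives no hormone mean, SD, age trend or visit-to-visit correlation. No numerical bias can be derived for this analysis.

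**3. The general claim about random effects.** This part concerns a different setting, the regression of one measured variable on another. It shows only that the claimed property is absent. Take two visits, a true slope of 0, and an unmeasured child factor explaining a share r of the variance of both variables (r is an assumption).

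- Covariance of the two child means: r
- Variance of a child mean: r + (1 − r)/2 = (1 + r)/2
- Between-child slope: r ÷ [(1 + r)/2] = 2r/(1 + r)
- Within-child slope: 0

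The random-intercept estimate is a weighted mean of the last two:

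| r (assumed) | Between-child slope 2r/(1+r) | Random-intercept estimate (1,000 simulations) | Within-child estimate |
|---|---|---|---|
| 0.2 | 0.4/1.2 = 0.33 | 0.18 | about 0 |
| 0.3 | 0.6/1.3 = 0.46 | 0.26 | about 0 |
| 0.5 | 1.0/1.5 = 0.67 | 0.44 | about 0 |

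Adding a random slope does not cure it. With four visits, 300 children, confounder and noise SDs of 1, and 12 replicates, the intercept-plus-slope model gave 0.30 for a constant confounder. It gave 0.54 when the confounder also had a child-specific trend (SD 0.5 per visit). The truth was 0 in both. In the second case even the within-child estimate was 0.28.

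**The case against.** **The sentence is harmless where it first appears.** This stands. It describes the models for aims 1 and 2, where randomisation deals with unobserved confounding and random effects suit repeated measures. A reader might infer that the BMI z-score result is at risk; the document does not support that.

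**Simulated bias says nothing about a paired contrast.** This stands too. A reader might carry the 0.18 to 0.44 over to gut hormones. Those figures come from assumed confounding in an exposure-outcome regression, whereas child-constant factors cancel in complete before/after pairs.

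**The before/after wording may be shorthand for comparing changes between arms.** This is possible. Mann-Whitney is a test for independent groups, controls are measured at the same visits, and the central hypothesis is comparative. It cannot be said that the analysis will certainly ignore arm. But the text as written names only before and after, and if arms are meant, randomisation gives the protection and the claim about unobserved confounders is still wrong.

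**Age is already a covariate.** This helps only partly. Baseline age leaves the average within-child change untouched. Age at visit removes ageing only if differences between children of different ages mirror change within a child. Neither handles secular trend or regression to the mean.

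**The dietary model is a validation.** This largely stands. "including, again, the confounders" carries the claim only by reference. A child's habitual diet drives both measures, so shared between-child variation may be the very agreement sought. A reader might conclude that only the within-child coefficient should count; that could discard what aim 4 needs.

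**Conclusion.** The statement that the random intercept and slope control constant and time-varying unobserved confounders is wrong, and it is explicitly repeated for gut hormones. Followed as written, the before/after hormone estimate keeps the whole of δ: it is δ + τ in the intervention arm, or δ + τ/2 with arms pooled, despite the stated adjustment. The size of δ is unknown from the document.

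The conclusion rests on reading the gut-hormone sentence literally, and the cancellation of child-constant factors assumes complete pairs. It does not touch the primary outcome or the randomised comparisons of aim 2. For the dietary-biomarker model the consequence is one of description: the result may not be called adjusted for unobserved confounders, but the document does not support calling the analysis itself invalid. The point is worth correcting because a sound alternative uses data already planned.

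**What to change.** 1. In the main model description, say that the random intercept and slope account for within-child correlation and for differences in trajectory. Delete the claim that they control unobserved confounders, and delete the reference to unobserved confounders in the gut-hormone sentence.
2. Make the gut-hormone analysis the between-arm difference at 9 months, adjusted for the baseline value, country and the listed covariates. State that it applies to children with optional blood samples. The Study design section places randomisation after baseline assessment, so the baseline-sampled group is formed before allocation. Samples missing at 9 months are not protected in that way, so report their number by arm.
3. Describe the dietary-biomarker and metabolite result as an association adjusted for measured covariates only. Within- and between-child coefficients may be reported together, without making the within-child one the sole result.

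**Cost.** Items 1 and 3 are wording, plus one model term if the coefficients are split. Item 2 needs no new data but gives up some precision. With n children per arm, equal variance σ² at both visits and correlation ρ, the one-arm before/after mean has variance 2σ²(1 − ρ)/n. The baseline-adjusted arm difference has 2σ²(1 − ρ²)/n, which is (1 + ρ) times as large. For assumed ρ of 0.3 to 0.7 the standard error is √1.3 = 1.14 to √1.7 = 1.30 times as large. That is the price of an estimate that isolates τ.
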